### Missing data considerations

The difficulties in dealing with missing data are often increased in the case of subjective data collected using questionnaires because missing data are often informative in this case. Indeed, we often observe that as health deteriorates, the risk of non-responses increases and missing data are therefore not random (missing not at random or MNAR). The analysis of MNAR data is truly problematic because it can lead to biased and inaccurate estimates of RS and of the true change of the subjective criteria one is trying to assess [42, 43]. Yet, methods such as SEM assume non informative missing data, that is to say missing at random (MAR) or completely missing at random (MCAR) data, unlike IRT models that can handle non-random missing data. The interest of IRT models was highlighted in cross-sectional and longitudinal studies [44–47]. These models were more powerful and allowed obtaining unbiased estimations of the effects of interest even in case of MNAR data, while models based on the observed scores showed poor properties in terms of bias and power estimates. The potential of using models coming from IRT, instead of or in addition to SEM models in the field of RS was also emphasized from a conceptual point of view [18, 48]. However, the formal assessment of the relative performance of SEM and IRT models in case of missing data has never been done to our knowledge. Hence, identification of the best methodological approach for RS detection in presence of missing data is still unknown. As stated in the Statistical analysis section, IRT and SEM will be used as complementary analysis and they will be also used to perform sensitivity analyses to assess the robustness of results.

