### Primary outcome measure

The primary outcome will be the change in QoL, taking into account the possible occurrence of response shift. This criterion will be measured by a specific questionnaire ReTransQol developed for kidney transplant recipients [24]. It will be evaluated every 6 months prior to surgery, at hospital discharge, and three months, six months, one year and two years after the transplantation.

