### Statistical analysis

Recipients will be described according to both groups, PPT and PDT. Such descriptive analyses will be performed on the main socio-demographic and clinical variables, either related to the recipient (except for the gender which is a matched between both groups), the donor or the transplantation. Categorical variables will be compared using Mac Nemar Chi2 tests for matched data. Continuous variables will be compared using a Student’s t-tests for paired data. This step will be important to assess the heterogeneity of the two populations and to identify possible confounding factors.

Structural equation models (SEM) and models coming from Item Response Theory (IRT) will be used to analyze changes in QoL and psychological dimensions (subjective well-being, perceived anxiety and depressive disorders, perceived stress) including the detection of response shift (RS) occurrence and its adjustment in the analyses, where appropriate, to estimate true changes. SEM and IRT will be used as complementary methods since SEM is appropriate for detecting RS at the dimension level (e.g. the “Physical Health” dimension of the RetransQoL) and IRT is appropriate for detecting RS at the item level within a dimension (e.g. the item “You are as well as anyone else” in the “Physical Health” dimension of the RetransQoL). SEM models [36] often include variables that are not directly observed (latent variables corresponding to QoL dimensions for instance) and possible links between these and the observed variables (observed scores for each QoL dimension). IRT models belong to the family of generalized linear random effects models [37]. They describe the probability of responding to each response category of a given item as a function of the latent variable one is trying to measure (patient’s “true QoL”) taking into account the psychometric characteristics of the scale through the questionnaire’s items parameters. Identification of RS and “true change” estimation (change in the subjective criterion being studied taking RS into account) will be performed in the following way: SEM analyses will follow the iterative algorithm developed by Oort [38] and IRT analyses will be done using a specific iterative algorithm called the RespOnse Shift ALgorithm in Item response theory (ROSALI) that has been recently developed [39].

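### The plan says without limit that IRT handles MNAR data and offers IRT with SEM as its sensitivity analysis, but for wholly missed questionnaires both rest on the same MAR assumption

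*Protocol article*

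**What the plan says.** The primary endpoint is longitudinal: "The primary outcome will be the change in QoL, taking into account the possible occurrence of response shift". It is measured before surgery, at discharge, and at 3, 6, 12 and 24 months.

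Missing data considerations sets out the expected mechanism: "we often observe that as health deteriorates, the risk of non-responses increases and missing data are therefore not random". It then separates the two model families. On one side, "methods such as SEM assume non informative missing data, that is to say missing at random (MAR) or completely missing at random (MCAR) data". On the other, IRT is introduced with "unlike IRT models that can handle non-random missing data", and cited work is summarised as showing that these models "allowed obtaining unbiased estimations of the effects of interest even in case of MNAR data". Neither statement distinguishes items skipped within a returned form from forms never returned.

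The section also carries a reservation: "the formal assessment of the relative performance of SEM and IRT models in case of missing data has never been done to our knowledge". It closes by saying of IRT and SEM that "they will be also used to perform sensitivity analyses to assess the robustness of results". It names no other sensitivity analysis for missing data.

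Statistical analysis describes the models themselves: "IRT models belong to the family of generalized linear random effects models". They give the probability of each response category given the latent variable. SEM is assigned to the dimension level and IRT to the item level. No model for the probability of non-response appears in either section.

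**The concern.** An IRT model gains over a score-based model when a form comes back partly completed, because the answered items still inform the latent value at that visit. That advantage disappears when the whole form is missing. The plan's own mechanism (sicker patients respond less) and a schedule running to 24 months make missed forms plausible.

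For such forms the stated robustness check changes the measurement level but leaves the missing-data assumption alone. Two methods that agree because they share an assumption would look like reassurance on the very problem the section calls problematic.

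The study hypothesises that PPT patients have lower quality of life and adapt less well. If poorly adapted PPT patients return fewer forms, or if the dependence on quality of life is steep, the error runs towards concealing the deficit being sought.

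**Working it through.** **Document figures.** Planned size: 130 × (1 + 2) = 390, as stated under Sample size. The article gives no missing-data rate, SD, effect size or power, so there is no bias figure of its own to reproduce. Every simulation input below is an assumption.

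**The likelihood.** With O(i,t) the set of items answered by patient i at visit t, the marginal IRT likelihood is

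L(i) = ∫ ∏ₜ ∏_{j∈O(i,t)} P(y(i,t,j) | θ(i,t)) f(θ(i)) dθ(i).

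If O(i,t) is empty, the inner product is 1 and θ(i,t) is integrated out. What remains comes from the patient's other visits and the group distribution. That is valid only if missingness does not depend on θ(i,t) given the observed data, which is MAR. Full-information SEM makes the same assumption at score level.

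**Simulation inputs.** 8 binary Rasch items with known difficulties and no response shift (both favour IRT); latent SD 1; two occasions, correlation 0.6; first occasion complete; PPT:PDT 1:2; N = 30,000 per scenario. Missingness at the second occasion: logit P = c − k·θ₂. IRT was fitted by marginal maximum likelihood. SEM was represented by bivariate-normal full-information ML on dimension scores, with bias converted to latent SD. A score was set missing if any item was missing.

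**Results: bias in estimated change (latent SD).**

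| Scenario (true PPT − PDT difference) | Forms missing PDT/PPT | IRT: PDT, PPT, difference | SEM: PDT, PPT, difference |
|---|---|---|---|
| None missing (−0.3) | 0/0% | −0.008, −0.024, −0.016 | −0.008, −0.024, −0.016 |
| Whole form, MAR (−0.3) | 30/30% | +0.001, −0.009, −0.010 | +0.002, −0.008, −0.011 |
| Whole form, k = 0.5 (−0.3) | 25/28% | +0.096, +0.073, −0.024 | +0.098, +0.074, −0.024 |
| Whole form, k = 1 (−0.3) | 25/30% | +0.185, +0.182, −0.003 | +0.189, +0.186, −0.003 |
| Whole form, k = 1 (−0.5) | 26/33% | +0.184, +0.227, +0.043 | +0.189, +0.229, +0.040 |
| Whole form, k = 1.5 (−0.5) | 26/38% | +0.240, +0.365, +0.125 | +0.251, +0.372, +0.121 |
| Whole form, k = 1.5 PPT, 0.5 PDT (−0.5) | 25/38% | +0.086, +0.301, +0.216 | +0.091, +0.305, +0.214 |
| Single items, k = 1 (−0.3) | no whole forms; 70% with a gap | +0.082, +0.094, +0.012 | +0.625, +0.699, +0.074 |

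Simulation noise is about 0.02. In every whole-form MNAR row the two methods agree within about 0.01 SD, whether the shared error is small or large. They separate only in the single-item row.

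**Further whole-form runs, IRT.** With k = 1.5 in both groups and a true difference of −0.30, the contrast bias is about +0.07. With dependence on quality of life in PPT only, a true −0.30 is estimated at about −0.08 to −0.11, a bias of +0.19 to +0.22. With no true difference and PPT-only dependence, one run gave +0.155.

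**Type I error for a bias of 0.155 at n = 130/260.** Refitting the two-occasion Rasch model at that size with 25 to 26% missing gave an empirical SE for the difference in change of about 0.16 to 0.18.
- SE 0.16: 0.155/0.16 = 0.97; Φ(0.97 − 1.96) + Φ(−0.97 − 1.96) = 0.16.
- SE 0.18: 0.155/0.18 = 0.86; Φ(0.86 − 1.96) + Φ(−0.86 − 1.96) = 0.14.

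The rate is therefore about 14 to 16%, against a nominal 5%. It belongs to this size of bias, and a different slope would change it.

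**The case against.** The other side has good points.

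- **Delta adjustments and shared-parameter models normally belong in a SAP, and only a condensed article is shown.** This stands in part. A reader might infer that IRT with SEM is the study's only protection against MNAR. The article cannot show that; it shows only that no other is named here. The point does not rest on the omission, because the article states a property of IRT that fails for missed forms. A fuller SAP would not make that statement right.
- **The text never says whole questionnaires will be missing.** True. Nor does it limit the IRT claim to partly completed forms, and repeated visits to 24 months make both patterns likely.
- **The section admits that the better approach is unknown.** True, and it softens the tone. The admission concerns the relative merits of SEM and IRT, and it supplies no check that varies the missingness assumption.
- **The comparison is not empty.** This stands. A reader might infer that IRT/SEM agreement says nothing at all about missing data. The single-item row contradicts that: +0.08 to +0.09 for IRT against +0.63 to +0.70 for SEM under that scoring rule.
- **The group contrast may be unharmed.** This stands for an equal mechanism that is not steep: −0.02 to +0.04 in the runs above.
- **The sizes depend on invented inputs.** They do. Two occasions were simulated; the actual schedule has more, and earlier post-transplant forms would recover some information about missed ones.

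A reader might also compute a type I error near 30% from SE = √(1/130 + 1/260) = 0.107, giving 0.155/0.107 ≈ 1.44 and 1 − Φ(1.96 − 1.44) = 0.30. That SE assumes a fully observed, error-free outcome with SD 1. It ignores measurement error, the variance of a change, and the missing forms themselves.

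**Conclusion.** The concern holds for wholly missed questionnaires. As described, IRT has no more protection against MNAR from missed forms than full-information SEM, and agreement between them cannot show robustness to it. If SEM were run on complete cases, the pair would still contain no MNAR model.

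Under the stated assumptions, within-group change is overstated by roughly 0.1 to 0.2 SD at slopes of 0.5 to 1, and by more at steeper slopes. The PPT-PDT contrast is nearly unbiased if the mechanism is equal and not steep. It is biased by about 0.07 to 0.22 SD, against a PPT deficit, if the mechanism is steep or differs by group. If PPT alone is affected and the bias is 0.155, type I error is about 14 to 16%.

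A reader might infer that the sought effect will be hidden. The documents do not support that: it needs steep or group-specific whole-form MNAR at substantial rates, and the article gives no rate and describes a general mechanism, not a PPT-only one. The point merits correction because the stated property is too broad and the named check does not test it. It does not show that the study's result will be wrong.

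**What to change.** 1. In Missing data considerations, limit the statement about IRT and MNAR to item non-response within returned forms, and say that IRT reduces bias there without necessarily removing it.
2. Add an MNAR sensitivity analysis for missed questionnaires on the primary endpoint. Either use delta-adjusted pattern-mixture imputation of latent quality of life, with separate deltas for PPT and PDT and a tipping point, or a shared-parameter model linking latent quality of life to drop-out. Group-specific deltas matter because the contrast is most sensitive to a mechanism that differs between groups.
3. Use the dates of death and return to dialysis already extracted from DIVAT (Table 1) as drop-out information.
4. Keep the IRT/SEM comparison, described as a check on measurement level and item non-response.
5. Report missing forms and missing items separately, by group and visit, so the reader can see which problem dominates.

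The cost is some extra analysis work. No new data, visits or patients are needed.

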## Ethical approval and registration

The study is registered with the ClinicalTrials.gov Registry (RC14_0078, NCT02154815), has approval from the ethical Committee for Persons’ Protection (CPP, Tours, 2014-S8), and from the advisory committee on research data and information in health (CCTIRS, Paris, 14.314).

## Discussion

The main assumption of our study is that preemptive kidney transplant recipients, who generally present a better level of health than patients undergoing dialysis, might although have a lower perceived quality of life and have more difficulties in adapting themselves to their new status. In contrast with the increasing number of studies in cancer, exploration of response shift has, to our knowledge, never been done in the context of ESRD despite its relevance in this disease, particularly in the context of preemptive transplantation. Our study will give more insight on the adjustment processes at hand in preemptive patients compared with patients with a quite short period under dialysis. Thanks to this knowledge, it might then be useful to organize a therapeutic educational program and psychological support specifically adapted for these preemptive patients before and following the transplant surgery. Exploration of the expectations of patients regarding transplantation could help personalize the specific aims of educational programs. It could increase the level of preparedness for transplantation and a better acceptance of its consequences. This point would be of major importance to prevent bad adherence to treatment if our results show that preemptive patients “regret” being transplanted because they are possibly not enough prepared to this new health status.

From a methodological point of view, the main limitation of our study may be the possible lack of comparability of the two groups that will be compared (PPT and PDT) despite matching on gender, center, and type of donor. To minimize this issue, all the statistical analyses, including all response shift analyses, will try to take into account confounding factors.

## Conclusion

The PreKit-QoL study is the first study which directly assesses the evolution of QoL and of other psychological criteria like anxiety or perceived stress of patients receiving a preemptive transplant taking patients’ adaptation into account through response shift analyses. We believe that this work may help providing a fresh perspective on expectations and care of transplanted patients, which may provide support for future research, care and preventive actions in the field of kidney transplantation. Our study might help to conceive specific and adapted individual and collective educational programs and psychological support in order to prevent a possible premature loss of the kidney as a consequence of non-compliance in patients that may be insufficiently prepared for transplantation.

## Abbreviations

QoL: Quality of Life
ESRD: End Stage Renal Disease
PPT: Patients with Preemptive Transplantation
PDT: Patients with Dialysis before Transplantation
PRO: Patient-Reported Outcomes
RS: Response Shift
GFR: Graft Filtration Rate
SEM: Structural equation models
IRT: Item Response Theory
MNAR: Missing Not At Random
MAR: Missing At Random
MCAR: Missing Completely At Random
